### **14.4 SECONDARY TARGET VARIABLES**

#### **14.4.1 INFLUENCE FACTORS (INFANT)**

- singleton or multiple pregnancy
- birthweight in gramm
- gestational age in days
- sex

#### **14.4.2 TARGET VARIABLES (INFANT)**

- APGAR (score 0-10)
- Admission temperature (°C)
- Intratracheal surfactant (yes/no)
- Blood transfusion during first 7 days of life (in ml per kg bodyweight)
- Peak IL-6 in 1st 24 h
- Peak CRP in 1st 24 h (mg/l)

- Peak bilirubin
- Peak haematocrit until discharge from hospital
- First measured normoblasts in 1st 24 h (given in normoblasts per 100 leukocytes)
- Neonatal complications:
  - Incidence of intubation and time duration of mechanical ventilation
  - Incidence of spontaneous Pneumothorax/Pneumoperitoneum
  - Incidence of any intraventricular hemorrhage (grades 1-4)
  - Incidence of periventricular leukomalacia or porencephaly
  - Incidence of BPD
  - Incidence of NEC with surgery
  - Incidence of spontaneous intestinal perforation (SIP) with surgery
  - Incidence of blood exchange transfusion due to critical hyperbilirubinemia
  - Incidence of retinopathy of prematurity (ROP) with treatment (drugs and/or surgery)
  - Highest ROP grade (1-5)
  - Incidence of plus disease in infants with ROP
- Incidence of cytomegalovirus (CMV) infection, verified by urine polymerase chain reaction (PCR)
- Incidence of infection with CMV requiring antiviral treatment with Valganciclovir and/or Ganciclovir
- Incidence of death in studied infants until discharge
- Bayley Scales of Infant and Toddler Development - Third Edition (Bayley-III) composite score (motor, cognitive, language) with 22-26 month corrected age

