### **7.2 HYPOTHESIS AND SECONDARY OBJECTIVES**

Hypothesis: EPT contributes to stabilization of preterm infants during neonatal resuscitation and provides improvement of neonatal outcome.

Therefore, the secondary aim of the study is to evaluate the influence of EPT on vital parameters and cerebral tissue oxygenation, the occurrence of neonatal morbidities, and long-term neurocognitive outcome compared to DCC.

Furthermore, we will investigate the hypothesis that EPT promotes lung growth and protects against BPD via an altered volume status, as well as via an increase in circulating growth factors and cytokines. The aim of the experimental part of the study is to characterize differences in the concentration distribution of angiogenic factors in serum between EPT and DCC. The second step is to investigate whether serum from placental blood and from children with and without ETP and DCC has a pro-angiogenic effect and stimulates lung vascularization.

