## **9.8 PROCEDURE IN CASE OF MISSING HEMATOCRIT MEASUREMENT**

If no hematocrit was determined in the first 24 hours of life (e.g. due to death of the participant within the first hours of life), the other target values of the study participant will still be recorded and evaluated separately.

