### **12.3 RECORDING TYPICAL COMPLICATIONS OF PREMATURITY**

The secondary outcome criteria include the typical complications of preterm birth. These include:

- Incidence of respiratory distress syndrome requiring:
  - Respiratory support (CPAP, positive pressure ventilation, non-invasive high frequency ventilation, invasive pressure ventilation, invasive high frequency ventilation).
  - Administration of intratracheal surfactant (invasive and less-invasive).
- Pneumothorax
- Pneumoperitoneum

- Incidence of IVH °I - °IV according to the criteria of Papile et al (16).
- Incidence of periventricular leukomalacia (PVL) and/or porencephaly
- Incidence of NEC (surgical or conservative treatment)
- Incidence of SIP (surgical or conservative treatment)
- Incidence of ROP requiring treatment
- Incidence of BPD, based on criteria defined by Walsh et al (17)
- Incidence of hyperviscosity syndrome caused by polyglobulia with impaired organ perfusion, defined as follows:
  - Polyglobulia characterized by a centrifuged hematocrit >65% or an Hb >22 g/dL in a peripheral venous blood draw and (at least one of the following points apply):
    - FiO2 requirement >0.3 for more than 12 hours without the presence of other causes such as: respiratory distress syndrome, pulmonary hypertension, vitium cordis, pneumothorax, infection.
    - Lactatemia of >3.0 mmol/l from peripheral venous or arterial blood gas analysis without presence of other causes such as: Vitium cordis, hemodynamically relevant persistent ductus arteriosus, metabolic disease, infection, acute hemorrhage, IVH
    - Reduced diuresis of < 0.5 ml/kg body weight per hour without the presence of other causes including: Infection, persistent ductus arteriosus, drug therapy with indomethacin or ibuprofen.

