### **14.2 STUDY POPULATION**

The primary analytic dataset is the intention-to-treat (ITT) population. This includes all randomized patients evaluated according to their assigned intervention. Only participants subsequently excluded according to section 9.5 are excluded. Intercurrent events are irrelevant for this treatment rule strategy (36).

The secondary evaluation dataset is the per-protocol (PP) population. This includes all patients included in the study who were treated and observed in a substantially protocol-compliant setting.

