### **14.3 PRIMARY TARGET VARIABLE**

The primary target variable is the mean haematocrit value in the first 24 hours after birth.

The hematocrit value is given as percentage. If there are > 1 measured values per patient, the arithmetic mean is determined. Group comparison is done by covariance analysis (ANCOVA) with fixed effects: baseline, group, gestational age (24+0 - 27 + 6 SSW vs. > 27+6 SSW) and gravidity (singleton vs. multiples). The influence of missing values is considered and explored via multiple substitutions (sensitivity analysis).

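### Section 14.2 sets all intercurrent events aside and 14.4.2 lists plain BPD incidence and ventilation time, so early deaths can make an arm look better on both

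*Protocol*

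**What the plan says.** Section 14.4.2 of the protocol lists incidence of BPD, "Incidence of intubation and time duration of mechanical ventilation" and "Incidence of death in studied infants until discharge" as separate infant variables. Section 12.3 takes the BPD definition from a cited source: "Incidence of BPD, based on criteria defined by Walsh et al (17". No section combines death with BPD, and none gives a time window or a rule for death for ventilation time.

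Section 14.2 fixes the primary analysis set: "This includes all randomized patients evaluated according to their assigned intervention". Only infants removed under section 9.5 are left out (an exclusion criterion found later, or consent withdrawn); death is not among those reasons. Section 14.2 then adds: "Intercurrent events are irrelevant for this treatment rule strategy (36".

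Two other places come near the question without answering it. Section 9.8 deals with an infant who has no haematocrit in the first 24 hours, for example because of very early death, and says "the other target values of the study participant will still be recorded and evaluated separately". Section 14.3 says "The influence of missing values is considered and explored via multiple substitutions (sensitivity analysis", but only for the primary variable.

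BPD carries a stated hypothesis. Section 7.2 proposes that "EPT promotes lung growth and protects against BPD via an altered volume status".

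**The concern.** BPD is a later complication; section 6.2 places it after the initial respiratory distress. An infant who dies early cannot reach it. Time on the ventilator likewise ends when the infant dies. A treatment-policy approach uses whatever value is observed regardless of what happened in between, but after death there is no value to observe. If all randomised infants are kept and death is set aside with every other intercurrent event, early deaths lower apparent BPD incidence and shorten apparent ventilation.

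If EPT prevented early deaths, the infants it saved would join those at risk of BPD and long ventilation, and EPT would look worse on both. If EPT caused early deaths, it would look protective on both. Because section 7.2 names protection against BPD as a hypothesis, a reader could take either pattern as evidence about the lung.

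**Working it through.** **1. Figures in the plan.** The protocol states none for BPD, ventilation or death. Its haematocrit sample size reproduces: 52.1 (SD 6.6) versus 57.31 (SD 7.26), unequal-variance t test, two-sided 5% (inferred from the 95% intervals in 14.1), gives 80.2% power at 29 per arm. Nothing below affects it. Every rate that follows is an assumption for illustration; only the arm size of 30 comes from the protocol.

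**2. BPD over all randomised infants.** Let p be the risk of death before BPD assessment and b the BPD risk in survivors.

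- Crude BPD = b(1 − p), which falls as deaths rise.
- Death or BPD = p + b(1 − p), which rises as deaths rise.

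With b = 25% in both arms, p = 10% (DCC) and p = 3% (EPT):

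- Crude BPD: 0.25 × 0.90 = 22.5% versus 0.25 × 0.97 = 24.25%. EPT looks 1.75 points worse.
- Death or BPD: 10% + 22.5% = 32.5% versus 3% + 24.25% = 27.25%. EPT is 5.25 points better.

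Swapping the death risks between arms swaps the picture. In whole infants, with 30 per arm and equal b in both arms:

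| b | Deaths | Crude BPD | Death or BPD |
|---|---|---|---|
| 20% | 0 vs 3 | 20% vs 18% | 20% vs 28% |
| 30% | 0 vs 3 | 30% vs 27% | 30% vs 37% |
| 40% | 0 vs 3 | 40% vs 36% | 40% vs 46% |
| 20% | 1 vs 6 | 19.3% vs 16.0% | 22.7% vs 36.0% |
| 40% | 1 vs 6 | 38.7% vs 32.0% | 42.0% vs 52.0% |

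The arm with more deaths looks 2 to 4 points better on crude BPD with three extra deaths, and 3.3 to 6.7 points better with five.

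**3. BPD among survivors only.** If those who die have the same BPD risk as the rest, this denominator gives b in both arms and there is no bias. If they are at higher risk, bias remains. Suppose 9 of 30 infants would develop BPD and 3 of those 9 die first. BPD falls from 9/30 = 30% to 6/30 = 20% over all randomised, and to 6/27 = 22.2% over survivors. Death or BPD stays at (3 + 6)/30 = 30%.

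**4. Ventilation time.** Take nine ventilated infants at 20 days each, with the other 21 never ventilated and surviving. If 3 of the 9 die on day 2, the mean among ventilated infants falls from 20 to (6 × 20 + 3 × 2)/9 = 14 days, an apparent gain. Ventilator-free days to day 28, with death = 0, go from (21 × 28 + 9 × 8)/30 = 22.0 to (21 × 28 + 6 × 8 + 3 × 0)/30 = 21.2, a loss.

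**5. Size against chance.** At 25% BPD and 30 per arm, the standard error of the difference is √(2 × 0.25 × 0.75/30) = 0.112, about 11 points. The differences in step 2 are well inside that.

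**The case against.** A reader might infer that the protocol scores an infant who dies early as BPD-free, and that such an infant gets the best score. The documents do not support either. No section states that scoring rule. The BPD definition rests on a cited source that is not at hand, and an infant who dies first could be treated as missing or not assessable. Nor is the score the best: on BPD the infant ties with every survivor without BPD, on ventilation a never-ventilated survivor has zero days, and the infant still counts under intubation and death.

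Further points on the other side have weight:

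- Denominators for individual secondary variables are often left to the SAP, which is not shown, so the absence of a rule would not by itself be a finding.
- Section 14.1 calls the analysis largely descriptive.
- Deaths are listed beside BPD in 14.4.2 and summarised for both arms every three months under 12.4.
- Section 9.2 excludes fetal or maternal compromise, and section 6.3 reports very high survival at this centre, so death risks of 10% may be too high.
- A death-or-BPD composite can be driven by deaths unrelated to lung growth.
- Death also truncates other variables in 14.4.2, such as treated ROP and the Bayley scores.

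These points limit the size and rank of the concern. They do not remove it, because the point rests on what 14.2 and 14.4.2 fix: the choice of variables, the all-randomised set, and a blanket sentence on intercurrent events that cannot work for death. Section 9.8 does not fill the gap, since it covers only infants without a haematocrit and does not say how their values are evaluated.

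**Conclusion.** The concern holds as an improvement worth making to secondary variables. Read literally, 14.2 and 14.4.2 together let early death reduce apparent BPD incidence and ventilation time, so both can favour the arm with more early deaths. Analysing survivors only removes the BPD bias only if death is unrelated to BPD risk. The separate death row lets a careful reader see the problem but does not correct the two variables.

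The true size is unknown because the protocol gives no death, BPD or ventilation rates. Under the assumed rates the shift in crude BPD is a few points (up to 10 if the infants who die are those who would have developed BPD), which is well within chance at 30 per arm. The primary haematocrit outcome and the sample size are not affected.

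**What to change.** - **Section 14.4.2, BPD:** add death before BPD assessment or BPD beside BPD incidence, and show both components by arm.
- **Section 14.4.2, ventilation:** add a measure that accounts for death, for example ventilator-free days to day 28 with death by then = 0. Keep raw duration, reported separately for survivors and for infants who died.
- **Section 14.2:** limit the sentence on intercurrent events to non-terminal events. This also opens the way to a stated rule for the other variables that death truncates.

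The cost is wording and two derived variables from data already collected. The composite mixes two events and can move because of deaths that have nothing to do with lung growth. Ventilator-free days does not distinguish ventilation beyond day 28. For both reasons the new measures should stand beside the components and the raw duration, not replace them.

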## **14 STATISTIC**

### **14.1 STATISTICAL AND ANALYTICAL PLAN**

Quantitative target values are described with the number of valid and missing values, mean, standard deviation and percentiles (0, 25, 50, 75, 100 (%)), qualitative target values with absolute (n) and relative (%) frequency. In broad aspects, the statistical analysis is based on a descriptive analysis. P-values are to be interpreted two-sided (exceptions are marked), accordingly two-sided confidence intervals (to the 95% level) are given.

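### Plus disease is counted only among infants who develop ROP, a post-randomisation event, so its between-arm comparison is not protected by randomisation

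*Protocol*

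**What the plan says.** Section 14.4.2 of the protocol lists three ROP items among the neonatal complications:

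- "Incidence of retinopathy of prematurity (ROP) with treatment (drugs and/or surgery", with no restriction on the denominator;
- "Highest ROP grade (1-5", a scale on which no value is written for an infant without ROP;
- "Incidence of plus disease in infants with ROP", which names its own denominator.

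The incidence of any ROP is not listed. The complications list in section 12.3 has one ROP entry, "Incidence of ROP requiring treatment".

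Section 14.2 makes intention-to-treat the primary analysis set: "This includes all randomized patients evaluated according to their assigned intervention". Section 14.1 sets the general approach, "In broad aspects, the statistical analysis is based on a descriptive analysis", and also provides for two-sided p-values and 95% confidence intervals. Section 7.2 states the secondary hypothesis that EPT improves neonatal outcome and names neonatal morbidities as something to be compared with delayed cord clamping (DCC).

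**The concern.** Under section 10.2.1.1 the randomisation envelope is opened before the caesarean section, so any diagnosis of ROP comes after allocation. ROP is also one of the morbidities that the trial's own hypothesis allows EPT to influence. Restricting plus disease to infants with ROP therefore selects each arm's denominator by an outcome of treatment. Stratified randomisation balances the arms as allocated; it does not balance the subsets that go on to develop ROP.

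What is at stake is how one line of the results table is read. If EPT mainly prevents the milder disease, the few EPT infants left in the denominator are the more severe ones, and a higher percentage in that arm could be taken for harm. Because any ROP is not a listed outcome, nothing in the list draws attention to the difference in denominators. The protocol is not silent here: it fixes a denominator, so this is not simply a detail left to the statistical analysis plan.

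**Working it through.** **Is there a plan figure to reproduce?** The protocol gives no rate of ROP or plus disease and no calculation for either. Its only sample-size target, 29 evaluable infants per arm for hematocrit (section 14.7), reproduces: the unequal-variance t test gives power 0.802 at two-sided 5%, a level assumed from the 95% confidence intervals in section 14.1. It plays no part in this point.

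**Inputs, all assumed for illustration.** 30 infants per arm; control incidence of any ROP 20%, 40% or 50%; a quarter of ROP infants with plus disease.

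**Formula.** Let r be the control rate of any ROP and q the share of those with plus disease. Let EPT multiply the rate of ROP without plus disease by a, and the rate of ROP with plus disease by b.

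- Plus disease over all infants: DCC r·q, EPT r·q·b.
- Plus disease among ROP infants: DCC q, EPT q·b / [(1 − q)·a + q·b].

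The conditional rate does not depend on r. It exceeds q in the EPT arm exactly when b > a, that is, when EPT prevents proportionally more ROP without plus disease than with it.

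**Results with q = 0.25.**

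| a | b | EPT rate among ROP infants (DCC 25%) | Over all infants |
|---|---|---|---|
| 0.5 | 1.0 | 0.25/(0.375 + 0.25) = 40% | unchanged |
| 0.5 | 0.8 | 0.20/(0.375 + 0.20) = 34.8% | falls by 20% |
| 0.5 | 0.5 | 0.125/(0.375 + 0.125) = 25% | falls by 50% |
| 0.8 | 0.5 | 0.125/(0.60 + 0.125) = 17.2% | falls by 50% |

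In the second row the all-infant rate falls from 5% to 4%, from 10% to 8% and from 12.5% to 10% for r of 20%, 40% and 50%. The conditional rate rises to 34.8% each time.

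**As counts, 30 infants per arm.**

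- Plus disease unchanged: DCC has 15 infants with ROP and 4 with plus disease; EPT has 9 and 4. Among ROP infants this is 4/15 = 27% against 4/9 = 44%. Over all infants it is 4/30 = 13% in both arms.
- Plus disease reduced: DCC has 12 and 3; EPT has 5 and 2. Among ROP infants this is 3/12 = 25% against 2/5 = 40%. Over all infants it is 3/30 = 10% against 2/30 = 6.7%.

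**The grade item.** The same list writes "APGAR (score 0-10" with a zero, and turns another graded complication into an incidence, "Incidence of any intraventricular hemorrhage (grades 1-4". The ROP grade has neither a zero nor an incidence form. The text leaves open where an infant without ROP is placed; it does not say that the infant is excluded.

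**The case against.** The strongest reply is that section 14.4.2 is a list of recorded variables, that no between-arm test is specified for either ROP item, and that section 14.1 calls for absolute as well as relative frequencies. In the first example a reader would see four infants with plus disease in each arm. Treated ROP is listed beside it without restriction. Even 4/15 against 4/9 has a two-sided Fisher p of about 0.41, which would hardly support a conclusion of harm. All of this stands and limits the weight of the point. It does not remove it: percentages shown by arm are read as a comparison, and the denominator is stated.

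Three stronger readings are tempting, and the document does not support them.

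- A reader might infer that the grade item, too, is defined only in infants with ROP. The range 1 to 5 may simply name the classification, and a category for no ROP could be added at analysis. No section prescribes a mean grade either. If grade is treated as qualitative, section 14.1 leads to counts per grade, with no mean to reverse.
- A reader might infer a contradiction with section 14.2. That section defines who is analysed and in which arm. It does not promise a value of every variable for every infant; the Bayley-III score cannot exist for an infant who died.
- A reader might infer that a benefit will show as harm. The table above shows that this needs b > a. With equal relative effects the conditional rate does not move, and with a larger effect on plus disease it falls.

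**Conclusion.** The point holds for the plus-disease item. Its stated denominator is a post-randomisation outcome that EPT may change, so the contrast between arms is not a randomised one. It can differ in direction from the rate over all infants: with the assumed counts, 27% against 44% among ROP infants, but 13% in both arms overall. This rests on assumed ROP and plus-disease rates, since the protocol gives none, and on EPT preventing proportionally more ROP without plus disease than with it. It shows what can happen, not what is expected.

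For the ROP grade only a clarification is warranted. The effect is confined to a secondary, mainly descriptive outcome. The primary hematocrit analysis and the sample size are untouched, and ROP is not among the events given special attention for early termination in section 12.4.

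**What to change.** In section 14.4.2:

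1. Define the outcome as the incidence of plus disease among all randomised infants examined for ROP.
2. Report by arm the number who died before examination or were not examined. This denominator also depends on survival to examination, so those numbers must stand next to the result.
3. Keep the figure among ROP infants as description, with its counts and without a between-arm test.
4. As a minor clarification, give the highest ROP grade a range of 0 to 5 with 0 for no ROP, and report counts per grade over the same infants. The number with any ROP then becomes visible as well.

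The cost is a few words in one section. The protocol does not describe ROP screening, but recording the highest grade and treated ROP presupposes eye examinations. On that assumption little or no new data collection is needed, beyond recording for each infant whether an examination took place.

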#### **14.4.3 TARGET VARIABLES RECORDED IN PARTICIPANTS OF INTERVENTION (EPT) GROUP**

- Duration until cord clamping (sec)
- Weight difference placenta before/after EPT (g)
- Feasibility of EPT (Implementation of the intervention according to the randomization yes/no, statement of rationale in case of deviating procedure)

#### **14.4.4 TARGET VARIABLES RECORDED IN PARTICIPANTS OF CONTROL (DCC) GROUP AND FIRST TWIN**

- Time to umbilical cord clamping after DCC (sec).

#### **14.4.5 TARGET VARIABLES RECORDED IN SINGLETONS AND SECOND TWIN**

- Mean airway pressure at time points 1,2,3,4,5,6,7,8,9,10 minutes (for twins only second twin).
- Mean tidal volume at time points 1,2,3,4,5,6,7,8,9,10 minutes (in twins only second twin).
- Time to onset of spontaneous breathing (in seconds; in twins only second twin).
- Heart rate at time points 1,2,3,4,5,6,7,8,9,10 minutes (in twins only twin no. 2)
- SpO2 at time points 1,2,3,4,5,6,7,8,9,10 minutes (for twins only twin no. 2)

- rScO2 at time points 1,2,3,4,5,6,7,8,9,10,15,20,25,30,35,40,45,50,60 minutes, respectively (in twins only twin no. 2).

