10.2.1.3 PROCEDURE IN THE CONTROL GROUP DURING AND AFTER BIRTH

In the control group, delayed cord clamping (DCC) is performed by the obstetrician and neonatologist. As soon as the infant is born, the midwife or neonatologist receives the infant with the umbilical cord still intact and the APGAR clock is started. The infant will be dried and wrapped in warm towels or a sterile plastic bag (neoHelp, Vygon, Aachen, Germany) (for extremely premature infants < 1000 g birth weight). By using gentle tactile stimuli (careful stroking over the back/hands/feet), the infant's spontaneous breathing is stimulated. While performing DCC, the infant is held at the level of the maternal pelvis (=placental level) with the umbilical cord still intact, if possible. The cord is cut after at least 30 seconds, but should not extend beyond 180 seconds.

During this period, obstetrics and neonatology are allowed to stop the DCC procedure and perform an immediate umbilical cord clamping < 30 seconds (=ICC) if one of the following criteria is fulfilled:

|        |                                                                                                                                                                                                                                                                           |
|--------|---------------------------------------------------------------------------------------------------------------------------------------------------------------------------------------------------------------------------------------------------------------------------|
| Mother | 

– Hemorrhage, hemodynamic instability, or both.

– (not known) placenta praevia, placental abruption

                                                                                                                                       |
| Infant | 

– Requirement for immediate neonatal resuscitation on neonatal care unit (avital infant with no muscle tone, no spontaneous breathing > 30 seconds).

– Interrupted placental blood circulation (placental abruption, placenta praevia)

 |

Table 1: Clinical settings in which immediate umbilical cord clamping (ICC) should be considered in the control group (according to (38)).

After the umbilical cord has been cut by the obstetric physician, the infant is transferred to the neonatal resuscitation unit of the neonatology department.

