#### 10.2.1.4 PROCEDURE IN THE INTERVENTION GROUP DURING AND AFTER BIRTH

In the intervention group, the infant is delivered by obstetrics together with the placenta. Here, birth occurs either in the intact amniotic sac or, when the amniotic sac is open, by gently detaching the placenta from the uterus. In any case, the infant is transferred with the umbilical cord and placenta still intact by the obstetrician or midwife to the neonatal resuscitation unit of the neonatology department.

If the amniotic sac is still intact, the neonatologist opens it on the neonatal resuscitation unit.

Neonatal resuscitation is also provided according to the internal clinical standards: the infant is covered with an occlusive polyethylene wrap (NeoWrap™, Fisher&Paykel Healthcare Limited, Auckland, New Zealand) for temperature management, the infant is placed in the left lateral position (so-called "comfort position") and the neonatologist initiates respiratory support using a CPAP mask according to a standardized internal protocol. At the same time, the nurse establishes standardized monitoring, which includes transcutaneously measured blood oxygen saturation, heart rate, respiratory rate and respiratory volumes. An NIRS monitoring is also established, analogous to the procedure in the control group.

Additionally, a further staff member (neonatologist 2 or nurse 2 or midwife) stores the placenta in a sterile plastic bag (neoHelp, Vygon, Aachen, Germany) immediately after opening the amniotic sac or after transferring the infant to the neonatal resuscitation unit, where it remains until umbilical cord is clamped. The placenta is sterilely stored and weighed on a separate kitchen scale, then kept at a level of about 40 cm above the infant's umbilicus for EPT. The exact level depends on the length of the

infant's umbilical cord and can therefore vary individually. EPT is to be performed from the time the placenta is held up for a period of at least 1 minute but not more than 10 minutes. After umbilical cord clamping, placenta shall be weighed again on the separately provided calibrated kitchen scale and the weight documented.

The arrangement in the neonatal resuscitation of the intervention group is shown in Figure 2.

[figure not shown]

Figure 2: Arrangement in neonatal resuscitation of infants in the intervention group.

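### Section 14.4.5 fixes vital-sign, ventilation and rScO2 readings from minute 1 with no time zero, but control infants reach the monitor only after cord clamping, so the earliest between-arm comparisons are selected or age-mismatched

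*Protocol*

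**What the plan says.** Section 14.4.5 of the protocol sets the time points. For one variable it reads "Heart rate at time points 1,2,3,4,5,6,7,8,9,10 minutes (in twins only twin no. 2"). SpO2, mean airway pressure and tidal volume have the same ten minutes. rScO2 is to be taken "at time points 1,2,3,4,5,6,7,8,9,10,15,20,25,30,35,40,45,50,60 minutes, respectively (in twins only twin no. 2"). The list covers both arms and does not say from what moment the minutes run.

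Section 7.2 makes these variables part of a comparison with DCC: "the secondary aim of the study is to evaluate the influence of EPT on vital parameters and cerebral tissue oxygenation". Section 6.3 singles out cerebral blood flow in the first minutes of life as especially relevant.

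Section 10.2.1.3 describes the control arm. At birth the midwife or neonatologist "receives the infant with the umbilical cord still intact and the APGAR clock is started". During DCC, "the infant is held at the level of the maternal pelvis (=placental level) with the umbilical cord still intact, if possible". On timing: "The cord is cut after at least 30 seconds, but should not extend beyond 180 seconds". Then: "After the umbilical cord has been cut by the obstetric physician, the infant is transferred to the neonatal resuscitation unit". CPAP, SpO2, heart rate, tidal volume and NIRS are described only from that point on. Table 1 in that section allows clamping before 30 seconds for maternal bleeding or instability, for placental causes, or for an infant who needs resuscitation at once.

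Section 10.2.1.4 describes the EPT arm. The infant is carried to the unit with cord and placenta intact, and CPAP is started there. "At the same time, the nurse establishes standardized monitoring", and NIRS follows as in controls.

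**The concern.** In the control arm, whether an infant can have a reading at minute 1, 2 or 3 after birth depends on when the cord was cut. That is an event after randomization, and it can be driven by the condition of the infant or the mother. In the EPT arm the start of monitoring does not wait for clamping. A comparison at those minutes among infants who have a reading is therefore no longer a comparison of the randomized groups. Analysis by assigned arm (section 14.2) does not restore it, because the loss comes from who can be measured. The multiple-imputation provision in section 14.3 is written for the primary outcome only.

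At stake is how the secondary aim on vital signs and cerebral oxygenation is read, in the very minutes that section 6.3 stresses. A difference there could come from who was on the monitor and when.

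**Working it through.** The plan states no figure on this point, so there is none to reproduce. The check sets the procedures side by side and then shows how far the answer depends on quantities the protocol leaves open.

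**1. When can monitoring start?**
- Control: time of clamping (30 to 180 s, or under 30 s if clamped immediately) plus transfer and sensor set-up (section 10.2.1.3). No mask or monitor is described at the mother's side. Section 6 itself says that DCC usually delays respiratory support because bedside CPAP is not established.
- EPT: time to deliver infant and placenta, plus transfer, opening of the sac if it is intact, and set-up (section 10.2.1.4). Clamping time does not enter.

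**2. Time points at risk if minutes count from birth.** A window of 180 s spans minutes 1, 2 and 3. The upper bound is therefore 3 of 10 time points for heart rate, SpO2, mean airway pressure and tidal volume. For rScO2 there are 10 time points (minutes 1 to 10) plus 9 (15, 20, 25, 30, 35, 40, 45, 50, 60), in total 19, so the bound is 3 of 19.

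**3. Illustration of how many controls could be read.** Inputs: 30 controls (synopsis) and a clamping window of 30 to 180 s (section 10.2.1.3). Assumptions: clamping times are uniform over the range shown, there is a fixed lag L for transfer and set-up, and no infant is clamped before 30 s. With range lo to hi, the number measurable at minute m is

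30 × min(1, max(0, (60m − L − lo) / (hi − lo))).

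For example, minute 2 with L = 30 s and range 30–180 s gives 30 × (120 − 30 − 30)/150 = 12.

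| Assumed clamping range | Lag L | Min 1 | Min 2 | Min 3 | Min 4 |
|---|---|---|---|---|---|
| 30–180 s | 0 s | 6 | 18 | 30 | 30 |
| 30–180 s | 30 s | 0 | 12 | 24 | 30 |
| 30–180 s | 60 s | 0 | 6 | 18 | 30 |
| 30–60 s | 0 s | 30 | 30 | 30 | 30 |
| 30–60 s | 30 s | 0 | 30 | 30 | 30 |
| 30–60 s | 60 s | 0 | 30 | 30 | 30 |
| 60–120 s | 0 s | 0 | 30 | 30 | 30 |
| 60–120 s | 30 s | 0 | 15 | 30 | 30 |
| 60–120 s | 60 s | 0 | 0 | 30 | 30 |

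With full use of the window, minutes 1 and 2 are thin at every lag, and minute 3 is thin once there is any lag. If clamping clusters at 30 to 60 s, only minute 1 is affected, and only when the lag is above zero.

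**4. Who supplies the minute-1 control readings?** A control treated with DCC is clamped at 30 s or later. If transfer and set-up take more than 30 s, the first possible reading falls after 30 + 30 = 60 s. Every control reading at minute 1 would then come from an infant clamped before 30 s for one of the Table 1 reasons.

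**5. When is the last control measurable?** An infant clamped at 180 s has a reading by minute 4 if L ≤ 240 − 180 = 60 s, and by minute 5 if L ≤ 300 − 180 = 120 s.

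**6. If minutes count from arrival instead.** The selection goes, but minute 1 then means a different age in each infant. Within the control arm alone, permitted clamping times spread that age over 180 − 30 = 150 s. EPT infants arrive on a timetable unrelated to clamping, so the arms would be compared at different ages after birth.

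**The case against.** The best defence is that section 14.4.5 is a list of variables to record. It names no test or per-minute contrast. Section 14.1 calls the analysis largely descriptive and already promises counts of valid and missing values. Models and the handling of missing minutes may properly sit in an analysis plan that is not at hand. This stands as far as the choice of model goes, and no repeated-measures model is asked for here. It does not remove the conflict: the protocol itself fixes minute-1 readings in both arms, an EPT-versus-DCC aim, and a control procedure that cannot deliver those readings evenly. Counts of missing values would reveal the selection but not correct it.

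Three stronger readings are tempting, and the documents do not support them.
- **All EPT infants are compared with early-clamped controls only.** EPT infants also need transfer, sac opening and sensor placement. Section 7.3 expects that in 10–20% of elective cesareans the placenta cannot be delivered with the infant, and section 10.2.1.6 then follows control-group care. Early values will be missing in both arms. The asymmetry is that in controls this depends on clamping.
- **The bias favours EPT.** Table 1 includes maternal and placental reasons as well as a compromised infant, clamping at 30 to 60 s is fully compliant, and section 9.2 excludes known compromise and emergency section. EPT infants with very early readings may be selected too, for example by easy placental delivery. The direction is not established.
- **Three of ten time points are lost.** That is an upper bound. It needs clamping near the end of the window and some set-up time.

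It is also true that the control procedure starts an APGAR clock at birth, but section 14.4.5 does not tie its minutes to that clock. That leaves both horns of the problem open.

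**Conclusion.** The point holds in this form: sections 10.2.1.3, 10.2.1.4 and 14.4.5 do not fit together for the first minutes after birth. With a birth-based clock, between-arm differences at up to the first three minutes are subject to selection whose size and direction cannot be derived from the protocol. With an arrival-based clock, they are differences between infants of different ages. Either way those minutes do not support a comparison of the randomized strategies.

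The number of minutes affected rests on clamping times and set-up lag, neither of which is given. Depending on the assumptions in the table it runs from none (all clamping within 30–60 s and no lag) to all of minutes 1 to 3. From minute 4 every control can be on the monitor if set-up takes no more than 60 s, and from minute 5 if it takes no more than 120 s.

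This is a matter for correction before analysis, not a threat to the trial. The variables are secondary. The hematocrit outcome, the sample size and the later time points are not touched.

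**What to change.** Amend section 14.4.5 so that it agrees with sections 10.2.1.3 and 10.2.1.4:
- Define time zero as birth, on the same clock in both arms.
- Limit between-arm comparison to time points after the 180-second window plus set-up. Minute 5 onward is a workable choice (rScO2 from minute 5 to 60). Minute 4 would do if set-up is shown to take no more than 60 s.
- Report earlier minutes descriptively only, with the number of infants observed per arm at each minute, next to the clamping times that sections 14.4.3 and 14.4.4 already collect.

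This changes analysis wording only. It needs no new data and leaves delivery-room procedure as it is. The cost is giving up a between-arm comparison of the first minutes, which is unwelcome given the emphasis in section 6.3, but the design cannot support it.
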